### Tests and procedures during the study period

#### Intervention group (CRT-P)

These patients should follow a management algorithm as described in figure 1.

Patients with normal CRT at baseline will proceed to periodic monitoring (every hour/6 hours) and start the algorithm if CRT becomes abnormal at any of these timepoints. Patients with abnormal CRT will follow the loop when fulfilling the Sepsis-3 definition of septic shock. The first categorization will be performed according to pulse pressure.^(16,17,22)^ Patients with a pulse pressure < 40mmHg, will undergo fluid responsiveness assessment.

Fluid responsiveness assessments will be performed using the technique preferred by each center, but supplementary recommendations with technical details will be provided in the Manual of Operations.^(9,23-26)^ Passive-leg raising with pulse pressure may be acceptable in spontaneous breathing patients. However, considering the possibility of false negatives, it is not the preferred technique.^(9,26,27)^

Fluid responsiveness-negative patients or those with undetermined status should proceed to obligatory critical care echocardiography (CCE) to rule out significant cardiac dysfunction (Figure 1) and proceed accordingly.^(28,29)^ Fluid boluses (500mL of crystalloids or 5% albumin) will be administered in 30-minute intervals with a maximum of 1000cc (2 fluid challenges) provided that the patient remains fluid responsiveness-positive and no safety issues appear (increase in CVP > 5mmHg or other congestion signals). Patients with safety signals should proceed immediately to CCE (Figure 1).

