### Capillary refill time assessment

Capillary refill time will be measured by applying firm pressure to the ventral surface of the right index finger distal phalanx with a glass microscope slide. The pressure will be increased until the skin is blank and then maintained for 10 seconds. The time for return of the normal skin color will be registered with a chronometer. A CRT > 3 seconds will be considered abnormal.^(4,32,33)^

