### Standard care group

Patients allocated to the standard care group will be managed by the clinical staff according to standard practice at their sites, including decisions about hemodynamic and perfusion monitoring and all treatments, but should follow general recommendations of the Surviving Sepsis Campaign to avoid extremes of clinical practice.^(2)^ These recommendations include basic hemodynamic targets, such as a MAP > 65mmHg, HR < 120bpm, oxygen saturation (SatO_2_) > 94%, hemoglobin (Hb) > 7 - 8gr/dL, and the use of norepinephrine as the first vasopressor and crystalloids as the fluid of choice. All data regarding the insertion of invasive monitoring devices, intravenous-fluid resuscitation, vasoactive support, MV, and other supportive therapies will be collected by the study coordinator or monitors. Leading investigators at a site will not serve as the bedside treating physician for patients in the standard care group.

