The win ratio is calculated as the total number of wins in the experimental group divided by the total number of wins in the control group. A value greater than 1 indicates better outcomes in the experimental group. The bootstrap resampling method will be used to calculate the 95% confidence interval (95%CI) for the win ratio and P value for the hypothesis test.

We will assess the treatment effect on the primary hierarchical composite outcome according to the following subgroups: age (< or ≥ 65 years); APACHE II (< or ≥ 25 points); SOFA (< or ≥ 10 points); baseline lactate (< or ≥ 4mmol/L); baseline CRT (< or ≥ 3 seconds); septic shock source (lung *versus* abdominal *versus* urinary *versus* soft tissues *versus* bacteremia *versus* other); and MV at inclusion.

P values will be reported for the primary outcome analysis, and p values for interaction will be reported for the subgroup analyses; the remaining outcomes will be reported with the mean effect and 95%CI. Given the potential for type I error due to multiple comparisons, the findings for the analyses of the secondary and tertiary outcomes should be interpreted as exploratory. All tests are 2-sided with an α level of 0.05. All analyses will be performed with the latest version of R software (R Foundation for Statistical Computing).

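### The baseline CRT subgroup is cut at < or ≥ 3 s although the protocol defines abnormal as > 3 s, so patients at exactly 3 s are normal by definition but analysed in the high-CRT stratum

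*Protocol article*

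**What the plan says.** Three places in the protocol article bear on the point.

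- **Capillary refill time assessment** sets the definition: "A CRT > 3 seconds will be considered abnormal". Exactly 3 s is therefore normal. The same section says how the value is obtained: "The time for return of the normal skin color will be registered with a chronometer". It does not say whether whole seconds or decimals are recorded.
- **Intervention group (CRT-P)** ties management to that definition: "Patients with normal CRT at baseline will proceed to periodic monitoring (every hour/6 hours) and start the algorithm if CRT becomes abnormal". For the others, "Patients with abnormal CRT will follow the loop when fulfilling the Sepsis-3 definition of septic shock".
- **Statistical analysis** lists the subgroups for the primary hierarchical outcome, among them "baseline CRT (< or ≥ 3 seconds", and adds that "p values for interaction will be reported for the subgroup analyses".

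For the comparator, the Standard care group section sets no CRT threshold: "Patients allocated to the standard care group will be managed by the clinical staff according to standard practice at their sites".

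**The concern.** Abnormal CRT is not an inclusion criterion, so the trial will enrol patients on both sides of the threshold. Of the seven listed subgroup variables, baseline CRT is the only one that also decides whether a CRT-P patient starts the algorithm at time 0. The natural reading of a 3 s cut is therefore normal versus abnormal CRT. As written, the analysis draws that line one value away from where the protocol draws it.

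What is at stake is the interpretation of this one subgroup. The high-CRT stratum would mix patients whose CRT was abnormal at baseline with patients whose CRT was normal by the protocol's definition. The interaction p value would then test a contrast that differs from the one readers will assume. Interaction p values are among the few that the plan says it will report, so the result will be visible.

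**Working it through.** The plan gives no figure to reproduce here. The check has two steps.

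**1. Put CRT = 3 s through both rules.**

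| Baseline CRT | Protocol definition (abnormal if > 3 s) | Subgroup (< or ≥ 3 s) | Agree? |
|---|---|---|---|
| below 3 s | normal | low | yes |
| exactly 3 s | normal (3 > 3 is false) | high (3 ≥ 3 is true) | **no** |
| above 3 s | abnormal | high | yes |

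The rules disagree at exactly 3 s and nowhere else. No other text in the article reconciles them. Figure 1 was not available for this check.

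**2. Scale.** Let q be the share of all patients recorded at exactly 3 s and a the share above 3 s. The share of the ≥ 3 s stratum that is normal by definition is

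q / (q + a).

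The document gives neither q nor a, so **both are assumptions**. The total of 1,500 is from the Sample size section. With a = 50%:

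| q | Patients at exactly 3 s (1,500 × q) | q / (q + 0.50) |
|---|---|---|
| 0.5% | about 8 | 0.005 / 0.505 = 1% |
| 1% | 15 | 0.01 / 0.51 = 2% |
| 5% | 75 | 0.05 / 0.55 = 9% |
| 10% | 150 | 0.10 / 0.60 = 17% |
| 15% | 225 | 0.15 / 0.65 = 23% |
| 20% | 300 | 0.20 / 0.70 = 29% |

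The result is less sensitive to a than to q. At q = 10%, a = 40% gives 0.10 / 0.50 = 20%, and a = 60% gives 0.10 / 0.70 = 14%.

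The low values of q are what one would expect if the chronometer reading is entered with decimals. The high values are plausible if it is entered in whole seconds, because 3 s is then an ordinary recorded value. The patient counts cover both arms.

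**After the change.** With the subgroup cut at ≤ 3 s versus > 3 s, the middle row of the first table becomes normal/low, and no patient is classed differently by the analysis and by the definition.

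**The case against.** The best case against the point is that it is a matter of notation. Age, APACHE II, SOFA and lactate are listed in the same format, so the symbol may be a convention rather than a choice. The article does not say that the ≥ 3 s stratum is meant to hold patients who enter the algorithm. A detailed analysis plan is promised before database lock and could align the boundary. All of this limits the severity. It does not remove the contradiction, because both cut-points are stated outright and the article presents its statistical section as the core of that plan.

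A reader might also infer something stronger: that CRT-P patients at 3 s go untreated, that they dilute the effect in the high-CRT stratum by about the share computed above, and that the interaction test loses power as a result. The document does not support this, for three reasons.

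- These patients are checked hourly over the 6 hours and start the algorithm if CRT becomes abnormal. They are not untreated for the whole study period.
- Staying out of the algorithm can itself be a treatment contrast. The Introduction says that CRT guidance could limit unnecessary interventions, and the Sample size section rests the expected benefit on reduced fluid use. A control with the same CRT is managed by local practice. Neither the size nor the direction of any change in the subgroup estimate follows from the text.
- Being analysed apart from the group one was managed as applies literally only to CRT-P. Control patients have no CRT threshold, so for them the mismatch is only with the protocol's definition of normal.

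The unstated recording precision is not a fault of the article. That detail commonly sits in the case report form or the manual of operations. It matters here only because it determines the size of the problem.

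**Conclusion.** The point holds as a minor internal inconsistency. The subgroup boundary and the definition of abnormal CRT classify a patient at exactly 3 s differently, and this blurs the normal versus abnormal contrast in one subgroup and its interaction test.

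The misplaced share of the ≥ 3 s stratum could be anywhere from about 1–2% to about 17–29%. That range rests on two assumptions: 50% of patients above 3 s, and between 0.5% and 20% at exactly 3 s. At the low end the effect is negligible. These are shares of patients misplaced, not estimates of bias or of lost power. The mismatch itself is certain from the text, but its practical effect is not. The primary analysis, sample size and alpha do not depend on this cut.

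**What to change.** In the subgroup list, and in the statistical analysis plan, define the baseline CRT subgroup as ≤ 3 s versus > 3 s, so that it matches the definition in the CRT assessment section. This changes only the analysis and leaves the clinical rule as written.

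Make the change before database lock. A cut moved after results are known would look data-driven, and a cut left alone would have to be reported with an explanation of why it departs from the protocol's own definition. The cost is two symbols, with no change to data collection, visits or sample size.

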### Ethics and informed consent

Each investigator center will submit the study protocol to its Institutional Review Board (IRB). The study will start only after being approved by the IRB. Written informed consent will be obtained from a legal representative of all participants. This study follows local and international declarations. The informed consent form will be translated to all involved languages (countries).

### Trial organization and management

**Steering Committee:** the Steering Committee is responsible for the overall study supervision, assisting in developing the study protocol and preparing the final manuscript. All other study committees report to this committee. Its members are investigators trained in designing and conducting randomized clinical trials in critically ill patients.

**Advisory Board:** the Advisory Board is a committee of experts in the field that will advise the Steering Committee on different requested aspects and will also promote and organize substudies.

**Study Coordinating Center:** this Committee is the executive committee, conducting the trial in all organizational, logistic, and procedural aspects as well as controlling the DQT.

**Data Safety Monitoring Board:** the DSMB comprises independent epidemiologists and intensivists who supervise the trial.

Interim analyses will be conducted after recruitment of the first 200 patients and at 75% of the sample by the DSMB. The first interim analysis will have two steps:

- A safety analysis where 28-day mortality will be compared between anonymized groups masked as A or B to detect potential risks associated with the intervention. According to the results, the DSMB may recommend the interruption of the study for safety reasons.- A second blinded-to-outcome analysis will be performed to compare the use of selected procedural interventions such as resuscitation fluids during the 6-hour study period between groups to demonstrate a gradient. If no difference or gradient is found, the DSMB may recommend interruption of the study for futility reasons.

The second interim analysis will focus on differences in the primary outcome between groups to potentially recommend an earlier interruption of the study in case of an already statistically significant difference.

### Study Centers

Approximately one hundred centers will be recruited in Western Europe, Asia, North America, and Latin America. The process will start with a survey of professional and technical resources as well as processes of care. Centers will be contacted to make this process representative across public, private and university hospitals, different countries and cultures, and hospital sizes.

## DISCUSSION

ANDROMEDA-SHOCK-2 is a relevant study in septic shock for several reasons: it proposes a resuscitation strategy based on clinical phenotypes and CRT as a resuscitation target, allowing us to individualize therapy according to the patients’ clinical scenario; it will assess its impact on clinically relevant outcomes; and it will be conducted in a broad range of ICUs on approximately 4 continents, capturing different realities and expanding its external applicability. If our hypothesis proves to be correct, the processes of care of septic shock resuscitation can be optimized with bedside tools.

**Ethics approval and consent to participate:** Each investigator center will submit the study protocol to its Institutional Review Board (IRB). The study will start only after being approved by the IRB. Written informed consent will be obtained from a legal representative of all participants. This study will be performed in compliance with local and international declarations.

**Authors’ contributions:** All the authors helped in the design and the final manuscript draft. All authors read and approved this final manuscript.

